#### Supply of intervention

Trial interventions (including placebo) are provided as identical capsules bottled in participant-ID-labelled containers by a GMP-certified compounding pharmacy, Oxford Compounding (North Perth, Australia). The placebo capsules are comprised of microcrystalline cellulose with no active ingredients. No dose modification of the trial intervention is permitted. All capsules are lightly scented with garlic to avoid potential bias.

#### Discontinuing or modifying allocated interventions

If a participant decides to withdraw from the project, participants are asked to notify a member of the research team. If a participant withdraws consent during the research project, relevant project team members will not collect additional personal information from the participant. However, personal information already collected will be retained to ensure that the results of the research project can be assessed and to comply with the law. Participants will be made aware that data collected by the investigator team up to the time the participant withdraws will form part of the research project results.

#### Relevant concomitant care during the trial

Apart from the medications in the exclusion criteria above, participants will be able to continue their regular medically prescribed regimen. Participants will be encouraged to inform their general practitioners (GPs) that they are participating in this study. Participants should not partake in other clinical trials while participating in this study.

### Study procedures

Table 2, schedule of assessments, details the overall schedule of the trial.

**Table 2 Tab2:** LARGE trial schedule of assessments

	STUDY PERIOD					
Visit	Screening /enrolment	Visit 1 (informed consent)		Visit 2		Visit 3 (EoS)
TIMEPOINT	-t_1_ (1 day)	0 (1 day)	t_1_ (2 weeks)	t_2_ (1 day)	t_3_ (12 weeks)	t_4_ (1 day)
**ENROLMENT**:						
**Eligibility screen**	X					
**Informed consent**		X				
**Participant demographics**		X				
**Participant anthropometric measures**		X				
**Group allocation**		X				
**INTERVENTIONS**:						
**Placebo**			X		X	
**L-arg**					X	
**AGE**					X	
**L-arg + AGE**					X	
**ASSESSMENTS**:						
**Daily and weekly migraine diaries**			X		X	
**MSQ**		X				X
**SF-MPQ**		X				X
**L-VISS**		X				X
**VLSQ-8**		X				X
**OCTA**				X		X
**Acute light challenge**				X		X
**Blood markers**				X		X

L-arg = l-arginine; AGE = aged garlic extract; t = timepoint; MSQ = Migraine-Specific Quality-of-life Questionnaire; SF-MPQ = Short-Form McGill Pain Questionnaire; L-VISS = Leiden Visual Sensitivity Scale; VLSQ-8 = Visual Light Sensitivity Questionnaire – 8; OCTA = optical coherence tomography angiography

### Primary and secondary outcomes

#### Primary outcomes

The primary objective of the LARGE trial is to evaluate the effectiveness of oral supplementation of L-arginine, AGE or the combined treatment of oral L-arginine and AGE, in reducing the severity and frequency of migraine attacks in chronic frequent episodic migraines in adults. By chronic frequent episodic migraineurs, we include both episodic and chronic, as well as uncertain: from published official guidelines, some clinical trial participants may not fit neatly into having episodic or chronic migraines, and/or into with or without aura, but they are nonetheless included [25]. In accordance with the International Headache Society guidelines for RCTs in preventative treatment of episodic migraines in adults [23], the differences in the mean number of migraine episodes per month, between baseline (visit 2) and end of study (EoS; 12 weeks treatment, visit 3), will be determined as the primary outcome measure assessed by a standardised daily migraine diary (Appendix 3). Migraine frequency will be measured not just within each migraine day, but the number of migraine occurrence days over the weeks. From the daily migraine diaries, treatment efficacy will be evaluated by the mean change in outcome measures between baseline and EoS within each group, and thereafter compared with changes between each intervention group. Primary outcomes collated from the diaries include: (a) mean number of migraine episodes per month (migraine frequency); (b) mean number of migraine days per month; (c) mean number of moderate-or-severe migraine days per month; (d) mean duration of each migraine episode (hours) per month; (e) mean number of acute migraine medication doses per month; and (f) number and type of self-reported adverse events per month. We will not measure migraine episode duration, because the participant is able to use an abortive drug at any point, and sleep intervals can disrupt countability of each episode.

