### Trial design

This is a single-site, randomised, double-blind, parallel-group-design, placebo-controlled, phase-II clinical trial on the efficacy, safety and tolerability of oral L-arginine and/or AGE in 18-80-year-old individuals with chronic frequent episodic migraines, based in Perth, Western Australia (WA). Study participants and members of the research team will be blinded to randomisation of the intervention treatments.

The maximum study duration is 14 weeks with a 2-week placebo run-in followed by a treatment period of 12 weeks. Eligible participants will be randomised to one of four parallel treatment groups in a 1:1:1:1 ratio, using permuted block randomisation: placebo, L-arginine, AGE, and combined L-arginine and AGE. Factoring for up to 20% drop-out rate, we aim to recruit 240 participants with up to 60 individuals randomised to each of the four treatment groups. Figure 1 shows an overview of the study design for the LARGE trial. The trial is registered through the Australian New Zealand Clinical Trials Registry (ACTRN12621001476820).

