### Study intervention

#### Intervention description and adherence

This study consists of 2 phases, including: (a) a 2-week placebo run-in phase (week − 2 to 0); (b) a 12-week treatment phase (day 0 to day 84). The Diener and Tassorelli guidelines suggest that a 4-8-week screening phase is ideal to ensure diagnostic migraine criteria are met for both episodic and chronic migraines [23, 24]. However, since participants could benefit from 3 months’ treatment without a high attrition rate, 4–8 weeks’ placebo would already take up half the investigation time for each participant. We are relying on participant numbers to compensate to power the study, and we have already ensured diagnostic criteria are met, as all participants must have confirmation from a physician or neurologist that they have migraine. We have included the extensive list of eligibility criteria, including frequency of migraines participants must have to be included in the trial. Participants are asked to report any adverse effects that arise from the treatment, at absolutely any point during their time in the trial. They are contacted one week after each of visits 1 and 2 to reinforce this and to check treatment compliance. Leftover capsules are counted at the end of each participant’s 2 and 12 weeks, to check placebo and verum treatment compliance, respectively.

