Once individuals are deemed eligible according to the inclusion and exclusion criteria listed in Table 1, participants will be asked to provide written consent and will be enrolled into the trial. At the consent visit (visit 1), participants will be asked to provide basic demographic information, complete medical and migraine history (i.e., duration of migraine, age of onset, monthly migraine frequency), current medication, menstrual status if applicable, and medical history. Baseline demographic and anthropometric measures were adapted from the National Institute of Neurological Disorders and Stroke Common Data Elements (www.commondataelements.ninds.nih.gov) and the PhenX toolkit (https://www.phenxtoolkit.org/), respectively. During this visit, participants will be instructed on how to fill out the daily and weekly migraine diaries. All participants are required to undergo a 2-week placebo run-in and are required to take oral placebo capsules for 2 weeks (5 capsules per day). Thereafter, at visit 2 (baseline), a 12-week supply of the respective randomised treatment will be dispensed to each participant; 5 capsules a day for 12 weeks (placebo; L-arginine; AGE; combination of L-arginine and AGE). Participants are contacted one week following commencement of treatment, to discuss any potential adverse events and treatment compliance.

Each participant will be provided with a paper-based diary to improve adherence of all groups (see Appendices 2 and 3). Treatment efficacy in terms of headache pain, severity and frequency will be evaluated by a standardised daily migraine diary (Appendix 2) and a summarising weekly migraine diary to track clearer long-term progress (Appendix 3). A capsule information sheet is dispensed with the intervention capsules to provide details instructions on missed doses where relevant. Similar to the placebo run-in, participants will be required to return capsule bottles at the end of the 12-week intervention to determine adherence to treatment. Poorly compliant participants will be excluded from subsequent analyses.

Visit 3 will be an exact replica of visit 2, with the difference that no further capsules/diaries will be given, and the visit-1 long-term questionnaires will have been filled out again to compare with the results of the visit-1 ones. Blood biomarkers, photosensitivity tests and retinal scans will be compared between visits 2 and 3 to test differences due to treatment over the 12 weeks.

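### Self-reported adverse events are listed among outcomes scored as change from a 2-week placebo run-in, which is not a usable safety baseline

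*Protocol article*

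**What the plan says.** In the protocol article, the Primary outcomes section states that "treatment efficacy will be evaluated by the mean change in outcome measures between baseline and EoS within each group". A second step sets the changes of the four arms against one another. The time points are "between baseline (visit 2) and end of study (EoS; 12 weeks treatment, visit 3". The list that follows opens with "Primary outcomes collated from the diaries include" and ends with "f) number and type of self-reported adverse events per month". Nothing exempts this last item from the rule.

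The Trial design section gives the phase lengths: "The maximum study duration is 14 weeks with a 2-week placebo run-in followed by a treatment period of 12 weeks". Table 2 and the legend to Figure 1 place the daily and weekly diaries in both phases, starting after visit 1. The section on intervention description and adherence has all participants take five placebo capsules a day in the run-in and five study capsules a day afterwards.

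That section also asks participants to report adverse effects at any time in the trial, and adds: "They are contacted one week after each of visits 1 and 2 to reinforce this and to check treatment compliance". For the treatment phase it says: "Participants are contacted one week following commencement of treatment, to discuss any potential adverse events and treatment compliance". The Allocation section describes the run-in contact only as a text message about progress with the capsules.

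**The concern.** A safety outcome has been placed under a rule written for efficacy. For migraine frequency, change from a run-in has a meaning: the condition existed beforehand and treatment should reduce it. For adverse events, the useful question is whether more occur on active capsules than on placebo over the same period. A run-in rate does not help to answer it when the run-in is itself a period on capsules.

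Item (f) is the only adverse-event outcome the article states, and Trial design names safety and tolerability among the subjects of the trial. If the change is reported as described, a fall within an active arm could be presented as good tolerability when it reflects complaints from starting the capsules, looser follow-up on treatment, or chance in a 2-week count.

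**Working it through.** The article gives no adverse-event rate or related figure, so there is nothing of its own to reproduce here. The check uses the phase lengths and the contact schedule.

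**1. What the baseline is.** Diaries start after visit 1 and baseline is visit 2, so the baseline rate comes from 14 days on placebo capsules. The end-of-study rate comes from the treatment phase, up to 84 days. The article does not say whether the whole phase or only its last month is used; I take all 84 days and note the alternative in step 3. Complaints caused by starting five capsules a day fall in the 14 days and are netted out of the within-group change.

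**2. Scaling to a month.** With a 28-day month (assumption), one run-in event counts as 28/14 = 2.0 per month and one treatment event as 28/84 = 0.33 per month. A participant with one event in each phase therefore scores 0.33 - 2.0 = -1.67 per month. This does not bias the mean when the rate is constant, but it shows how strongly single run-in events drive the score.

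**3. Noise.** Assume independent Poisson counts at a constant daily rate λ.
- Variance of the on-treatment rate: λ/84.
- Variance of the change: λ/14 + λ/84 = 7λ/84, which is 7 times as large.
- If only the last 28 days are used: λ/14 + λ/28 = 3λ/28 against λ/28, which is 3 times as large.

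Stable differences between people reduce this penalty. If the daily rate varies between people with variance τ², the on-treatment rate has variance τ² + λ/84 while the change still has λ/14 + λ/84. The penalty is gone once τ² reaches λ/14.

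**4. Ascertainment in the two periods.**
- Scheduled staff contacts: 1 in 2 weeks (0.50 per week) against 1 in 12 weeks (0.083 per week).
- Daily diary entries: 14 in 14 days against 84 in 84 days, ratio 1.0.
- Weekly diary entries: 2 in 2 weeks against 12 in 12 weeks, ratio 1.0.

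Whether the contacts matter depends on reporting behaviour that the documents do not describe. Let a constant true rate be reported with probability p1 in a week with a contact and p0 in other weeks (assumption). Captured shares are (p1 + p0)/2 in the run-in and (p1 + 11·p0)/12 on treatment. The difference is 5(p1 - p0)/12. It is zero when p0 = p1. At the other extreme, p0 = 0, the captured share drops from p1/2 to p1/12, a fall of five sixths. Nothing in the article locates the trial between these limits.

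**5. Between arms.** The contact schedule is identical in all four arms and everyone is on placebo in the run-in, so run-in rates are equal in expectation. The difference between arms in mean change then has the same expectation as the difference in on-treatment rates. Incomplete capture multiplies both arms by the same factor: direction and rate ratio survive, and the absolute difference shrinks by that factor.

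**The case against.** The strongest reply is that the change rule speaks of treatment efficacy, that adverse events are not efficacy, and that a type of event cannot be averaged, so the change-score reading is only inferred from placement. That is fair as to intent. But (f) stands in the list without exception, and no other analysis of adverse events is stated, so a reader following the article would score it this way.

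Second, the Statistical methods section analyses continuous outcomes by analysis of covariance with the baseline value as covariate. Applied to (f), this would estimate the weight of the run-in rate instead of subtracting it in full, and would remove most of the noise penalty in the arm comparison. This stands. It does not rescue the within-group change, which the Primary outcomes section states separately.

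Third, detailed safety methods usually belong in the analysis plan, which is not shown. Their absence is no fault. The point here is a rule that the article does state.

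A reader might go further and infer that participants are prompted six times as often in the run-in, so that the adverse-event rate must fall in every arm. The documents do not support that. The ratio of six applies to staff contacts alone. The stated source of (f) is the diary, which is kept at the same frequency in both phases, and reports are invited at any time. Whether the diary forms carry an adverse-event item cannot be checked, because the appendices are not shown. No section says that adverse events are elicited at visits 2 and 3. A fall needs reporting to depend on contact, and an arm with a large enough true increase would still rise.

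**Conclusion.** The point holds in a limited form. As written, adverse events per month are scored against a 2-week rate on placebo capsules, and a within-group change from that rate is not interpretable as tolerability. This follows from the text and needs no assumption about reporting.

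The precision cost is a variance up to 7 times that of the on-treatment rate. It rests on the constant-rate Poisson assumption, full use of the 84 days and an unadjusted change score; it is smaller with covariate adjustment or stable differences between people. The effect of unequal staff contact has a plausible direction, towards lower reporting on treatment, but no derivable size; it may be nil. Neither feature favours any arm, and the randomised comparison keeps its direction and rate ratio. This is an inexpensive improvement in how safety is reported, not a threat to the trial's validity.

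**What to change.** In the Primary outcomes section and in the analysis plan, take (f) out of the outcomes scored as change from baseline. State that adverse events from visit 2 to visit 3 are compared between randomised arms, each against placebo: the share of participants with at least one event, and the event rate with time on treatment as exposure (for example, Poisson or negative-binomial regression with log days as offset). Report run-in events separately and draw no trend from run-in to treatment.

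This costs wording only and needs no new data. The downside is that run-in events appear only descriptively. The change does not improve capture on treatment: if reporting does depend on contact, the absolute difference between arms stays attenuated.

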#### Secondary outcomes

Secondary outcomes will comprise the changes in acute photosensitivity, quality of life (QoL), retinal vessel changes, and blood biomarkers of vascular tone, from baseline to EoS.

To explore the effects of each intervention arm relative to placebo on photosensitivity, a visual discomfort threshold will be determined via an acute light challenge on the second and third visits. Briefly, adapted from Woodhouse and Drummond (1993) [26], to determine the visual discomfort threshold, participants were subjected to an increased brightness of an LED panel facing them 200 cm away by 1% every 4 s. The percentage brightness of the Nanlite Mixpanel 150 RGBWW 150 W LED Panel (emission range: 0–11,320 lx) at which the participant expresses discomfort and requests no further increase in brightness will be recorded at both study visits and compared to determine differences if any, in visual sensitivity.

The self-reported Migraine-Specific Quality-of-life Questionnaire (version 2.1) (MSQ) [27, 28] and Short-Form McGill Pain Questionnaire (SF-MPQ) [29] will be completed by each participant at baseline and EoS. The MSQ is utilised to assess the change, before and after treatment, in each of the treatment groups in participants’ day-to-day functioning about impeding activity, preventing activity, and emotional feelings, that are usually affected by migraines. The SF-MPQ is used to evaluate weekly differences in pain intensity reported by each of the participants. The Leiden Visual Sensitivity Questionnaire (L-VISS) measures the impact of light and pattern sensitivity on daily functioning (“visual allodynia”) [30], and the Visual Light Sensitivity Questionnaire (VLSQ-8) measures the presence and severity of photosensitivity symptoms [31].

A number of recent studies have implicated lower vessel densities in the macula and optic nerve, as well as reduced thicknesses of the choroid and retina, in adults with migraines compared to controls without migraines [30–42]. Thus, an additional exploratory outcome will comprise the changes in retinal vessel density and the foveal avascular zone area measured via optical coherence tomography angiography (OCTA), with the AngioVue Imaging System (RTVue XR Avanti, Optovue Inc., Fremont, CA, USA), at baseline and 12-weeks post intervention, as a surrogate measure of cerebral vascular changes.

Moreover, blood biomarkers of vascular tone will be analysed in samples collected at baseline and EoS. Systemic concentrations of asymmetric dimethylarginine (ADMA) and symmetric dimethylarginine (SDMA), nitrates and nitrites, and endothelin-1, will be analysed in fasted plasma samples. Among our proposed panel of biomarkers, the antagonism between vasodilatory NO and vasoconstrictive endothelin-1 allows the assessment of potential changes in vascular tone [43]. Nitrates and nitrites are more stable derivatives of reactive NO in the bloodstream [44], and thus were chosen as a proxy measure of dilation of the vessels supplying the brain. ADMA and SDMA, additionally, would be valuable measures of interictal propensity to migraine, as higher levels of both vasoconstrictive molecules would reflect inhibition of vasodilatory NO production from L-arginine [43].

### Statistical analysis

#### Sample size and statistical power

We propose an RCT with a factorial treatment structure. This design is efficient and allows the estimation of both the main effects of L-arginine and AGE, and the interaction between L-arginine and AGE. This design with two factors at 2 and 2 levels has 4 arms/groups (treatment combinations). A total of 240 individuals are required to provide 60 subjects per group. This design achieves 87% power when an F-test is used to test factor L-arginine at a 5% significance level with the effect size of 0.2; achieves 87% power when an F-test is used to test factor AGE at a 5% significance level with the effect size of 0.2; and achieves 87% power when an F-test is used to test the L-arginine*AGE interaction at a 5% significance level with the effect size of 0.2. Cohen’s Effect Size Table [45] provides the interpretation of effect sizes as: Small: 0.1; Medium: 0.25; Large: 0.40. Our research study can therefore detect between small and medium effect sizes between each of the main effects and interactions. An estimated effect size of 0.2, used in the sample size calculation for testing the main effects and interaction, was obtained from our preliminary data. Assuming a dropout rate of 20%, a total of 300 participants will be initially recruited into the study, with 75 participants in each of the 4 treatment combinations.

### Allocation

Randomisation occurs on visit 1, in that the coded capsule bottle is picked up randomly and allocated to this next participant scheduled. One week after this first visit, they are texted to check progress on the capsules. We are using block randomisation: eligible subjects will be computer-randomised in blocks of 8, to one of the 4 treatment groups (placebo control, L-arginine, aged garlic extract (AGE), and L-arginine + AGE). Each participant will be randomised by participant ID, as this should preclude group allocation by order of study entry, as per the IHS guidelines [24, 25]. We will do this as the participants enter the trial, whereby the statistician will then have access to the list on the Research Data Capture (REDCap) tool where we will be entering all participant details and responses.

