#### Implementation

The randomisation schedule is sent to an independent pharmacist (Oxford Pharmaceuticals) who will then dispense trial intervention in blank packaging with only the participant ID displayed. The investigators will receive this by post and will supply each participant with the treatment pack on visits 1 and 2 (placebo for 2 weeks, then randomised treatment for 12 weeks).

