### Blinding

Although participants will be blinded to treatment allocation, we will inform them of the general nature and composition of the treatment prior to their participating. The investigator team will be blinded as to which treatment we are giving which participant, during the 12 intervention weeks. Only the statistician and pharmacist will not be blinded as to which participant receives which treatment, as they will be handling the randomisation schedules linking identification numbers to participant names. In case of emergency (an adverse event sustained by the participant, which requires medical treatment to know which study treatment has been given), the investigator will break the seal and be unblinded as to which treatment the participant has received. This will immediately be reported back to the investigator team and the HREC. The participant always has the option of dropping out of the trial.

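### The Allocation section describes two incompatible ways of assigning treatment, places assignment before the placebo run-in, and leaves the statistician unblinded

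*Protocol article*

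**What the plan says.** All references are to the protocol article.

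- **Mechanism, first description (Allocation).** "Randomisation occurs on visit 1, in that the coded capsule bottle is picked up randomly and allocated to this next participant scheduled".
- **Mechanism, second description (Allocation).** "eligible subjects will be computer-randomised in blocks of 8, to one of the 4 treatment groups", and "Each participant will be randomised by participant ID, as this should preclude group allocation by order of study entry".
- **Related sections.** Trial design specifies permuted blocks in a 1:1:1:1 ratio. Supply of intervention describes "identical capsules bottled in participant-ID-labelled containers". Implementation sends the schedule to an outside pharmacist, who is to "dispense trial intervention in blank packaging with only the participant ID displayed".
- **Timing.** Table 2 marks group allocation in the visit 1 column, in agreement with Allocation. Under Intervention description and adherence, "All participants are required to undergo a 2-week placebo run-in", and the randomised supply is handed out only at visit 2.
- **Who knows the allocation.** Blinding states: "Only the statistician and pharmacist will not be blinded as to which participant receives which treatment". Allocation adds that the statistician reaches the list through REDCap, the system in which participants' details and responses are entered.

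**The concern.** A permuted-block list balances the arms only if its positions are used in order. If site staff take whichever bottle comes to hand, the order of the list no longer governs assignment. A later reader then cannot tell from the protocol which procedure was followed. That matters for the running balance between arms and for the assurance that nobody influenced who received what.

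The timing adds a second, smaller cost. Everyone takes placebo for two weeks after visit 1. A person who leaves in that period belongs to an arm on paper but has never taken its treatment. The retinal imaging, light challenge and blood markers have their baseline at visit 2, so that person has none of these and no treatment-period diary. What remains is the visit 1 questionnaires and perhaps part of a run-in diary.

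Third, an analyst who can see the allocation alongside the responses has an avoidable opportunity to let it affect analysis decisions.

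**Working it through.** **1. Do the two descriptions agree?**

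| Question | Bottle pick | Computer list |
|---|---|---|
| What decides the arm? | Which coded bottle is taken | Position in a block of 8, linked to participant ID |
| What must be on the shelf? | Interchangeable coded bottles | A pack labelled for a given ID |
| Supported elsewhere? | No | Trial design, Supply of intervention, Implementation |

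If the ID is fixed before the visit, a pack bearing that ID cannot be a random pick for whoever comes next. If instead the bottle brings the ID with it, the arm still comes from the list, but the list is used out of order.

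**2. What does out-of-order use do to balance?** In a block of 8 with four arms, each arm appears 8/4 = 2 times, so the running gap between the largest and smallest arm never exceeds 2. For random picks from a pool of 4 × 60 = 240 bottles, a simulation of 2,000 sequences gave a median largest running gap of 12 (95th percentile 17). The protocol does not say how many packs are on the shelf at once. If staff picked only within one delivered block and emptied it before opening the next, the gap would stay at 2 or less. The effect therefore depends on the size of the pool.

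**3. The plan's power figure.** Inputs from Sample size and statistical power: N = 240, effect size f = 0.2, two-sided 5% F-test with 1 and N − 4 = 236 degrees of freedom. The noncentrality is N × f² = 240 × 0.04 = 9.6, which gives power 0.870. This matches the stated 87%. The recruitment figure also reproduces: 240/(1 − 0.20) = 300.

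**4. Does the timing of allocation change the power?** For a fixed number recruited, no. If 300 enter and 20% leave, 300 × 0.80 = 240 are analysed and power is 87.0%, whether the leavers were randomised or not.

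**5. How many randomised people might be lost in the run-in?** The protocol gives only an overall dropout of 20%. The share falling in the run-in has to be assumed.

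- Share in proportion to time, 2/14 = 1/7: 0.20/7 = 2.9%, or about 7 of 240 or 9 of 300.
- Share of one half: 0.20 × 0.5 = 10%, or 24 of 240 or 30 of 300.

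Nothing in the document favours a value in this range.

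**6. What would such losses do to arm sizes?** Start from 60 per arm with losses independent of arm (simulated):

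| Assumed run-in loss | Median gap, largest to smallest arm | 95th percentile |
|---|---|---|
| 5% | 3 | 6 |
| 10% | 5 | 8 |
| 20% (all dropout in the run-in) | 6 | 11 |

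**The case against.** The strongest defence is that the opening sentence of Allocation is merely loose. IDs may be tied to arms by the computer list, the pharmacist labels bottles by ID, and the participant receives a bottle and so its ID. On that reading the arm comes from the list and the ID on the bottle preserves a record of it. This is a possible reading, and it means that the audit trail need not be lost. It does not restore the order of the list. Nor can the pick be explained away as concerning only the placebo run-in bottle, because the sentence calls the act randomisation.

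A reader might infer that concealment is broken. The document does not support that. The capsules are identical and garlic-scented, the packs show only an ID, an outside pharmacist prepares them, and the investigators are blinded. Someone who sees only a code cannot choose by arm.

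A reader might also infer that run-in losses bias the comparison, or that later allocation would yield more analysed participants. Neither follows. Everyone takes placebo in the run-in and allocation is blinded, so losses should be unrelated to arm, and later allocation retains nobody extra. The visit 1 timing is stated consistently and is a design choice, not a contradiction.

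On the statistician, the access is openly disclosed, and nothing says that investigators can open the list on REDCap. Any compliance cut-off or final choice of model may be settled in a statistical analysis plan that is not at hand, so no criticism rests on those.

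**Conclusion.** The contradiction in the mechanism stands and should be corrected. As written, the bottle pick is incompatible with a block list used in sequence. The possible effect on running balance ranges from none (picks confined to one block at a time) to a median largest gap of 12 (picks from the full pool). If every bottle in that pool is used, the arms still finish at 60 each. The risk to concealment is limited.

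Allocating before the run-in is a lesser weakness. It depletes the randomised set and leaves the arms somewhat uneven, by a median of 3 to 6 people under assumed losses of 5% to 20% from 60 per arm. It is not expected to cause bias so long as the blind holds. The true run-in loss is unknown, so no single number of affected participants can be claimed.

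The unblinded statistician is an avoidable exposure and not evidence of bias. The stated reason for the access is handling the schedules, and the pharmacist already holds the schedule.

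**What to change.** - **Mechanism.** Delete the clause about picking a bottle. State that each participant receives the next sequential number on the computer-generated list. Reword the sentence on order of study entry to fit, since a concealed random list used in sequence does not let order of entry determine the arm. For people already enrolled, state which procedure was actually used.
- **Timing.** For participants not yet enrolled, assign the number at visit 2, after the run-in, and amend Table 2. The run-in bottles are all placebo and need no allocation code. For those already enrolled, report run-in losses by allocated arm.
- **Masking.** Keep the key with the pharmacist and off REDCap. Run the analysis on masked arm codes until database lock.

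The cost is a protocol amendment and relabelling by the existing pharmacy. Moving the allocation point also leaves two allocation procedures within one trial, which must be disclosed. Recruitment began in May 2021 and completion was expected in 2023, so the change of timing may reach few participants. The wording correction, the loss report and the masked analysis are worthwhile whatever the stage of recruitment.
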